### Sample size calculation

2.7

As the primary outcome to evaluate the efficacy of SSHT in patients with AD experiencing gastrointestinal disorders, this study will use the SCORAD scores. We calculated the sample size based on the previous study which evaluated the efficacy of Shiho Cheong gan-san for patients with AD.^[23]^ It is hypothesized that the mean changes of the SCORAD score in the SSHT and placebo groups after 4 weeks of intervention were 13.8 (μt) and 7.9 (μ*c)*, respectively and the standard deviations of the SCORAD scores between 2 groups were 8.2. A total of 60 participants, 30 in each group, are needed to achieve a statistical power of 80%, significance level of 0.05 in 2-tailed test, based on an estimated 20% dropout rate.

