### Statistical analysis

2.8

Appropriate statistical analysis methods will be used according to the type of measurement, number of associated factors and associations, as well as the distribution status. The software that will be used for statistical analysis is the SAS version 9.3 for Windows, at a statistical significance level of 0.05 and statistical power of 80%.

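### Sixty patients do not follow from the two-sided 0.05, 80% power and 20% dropout inputs in section 2.7: those inputs need 78 to 80, and 24 analysed per group gives about 68 to 70% unadjusted power

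*Protocol article*

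**What the plan says.** Section 2.7 (Sample size calculation) bases the calculation on an earlier study of another herbal preparation in atopic dermatitis. It assumes that "the mean changes of the SCORAD score in the SSHT and placebo groups after 4 weeks of intervention were 13.8", against 7.9 on placebo, and that "the standard deviations of the SCORAD scores between 2 groups were 8.2". It concludes that 60 patients in all, split equally between the arms, "are needed to achieve a statistical power of 80%, significance level of 0.05 in 2-tailed test, based on an estimated 20% dropout rate". The one sentence thus claims a two-sided test, 80% power and a dropout allowance together.

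Section 2.8 (Statistical analysis) repeats the target: "at a statistical significance level of 0.05 and statistical power of 80"%. That is the same claim restated, not a second error. Section 2.5 fixes 1:1 allocation. Section 2.9 makes the full analysis set the main efficacy population and plans baseline-adjusted analysis of covariance between groups. Section 2.7 mentions no baseline correlation and no reduction in variance.

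**The concern.** Section 2.7 gives every input to a standard two-group comparison of means, so the result can be checked without the source study or an unseen analysis plan. A standardised difference of about 0.72 needs slightly more than 30 evaluable patients per group for 80% two-sided power. If 30 is already the number randomised, it leaves no room for losing one patient in five.

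At stake is the stated power for the primary outcome. If 24 per group are analysed without adjustment, a true 5.9-point benefit would be missed about 3 times in 10, where the article implies 2 in 10. The type I error rate and the validity of the comparison are not affected. What is affected is how much weight a non-significant result can carry.

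**Working it through.** **Inputs (section 2.7 unless noted).** Difference 13.8 − 7.9 = 5.9. SD 8.2, taken as the common SD of change. Two-sided alpha 0.05, power 80%, dropout 20%, 1:1 allocation (section 2.5). Standardised difference d = 5.9/8.2 = 0.7195, so d² = 0.5177.

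**1. The stated calculation.** n per group = 2(z for alpha + z for power)²/d².
- Two-sided 0.05, 80% power: 2 × (1.960 + 0.8416)²/0.5177 = 2 × 7.849/0.5177 = 30.3, so 31 evaluable per group.
- With the noncentral t distribution, 31 per group gives 79.6% and 32 gives 80.9%, so 32 are needed.
- Dropout by n/(1 − 0.2): 31/0.8 = 38.75, so 39 per group and 78 in total. 32/0.8 = 40 per group, 80 in total.
- The looser inflation n × 1.2 gives 31 × 1.2 = 37.2, so 38 per group and 76 in total.

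None of these gives 60.

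**2. What does give 30 per group.**
- One-sided 0.05, normal approximation: 2 × (1.645 + 0.8416)²/0.5177 = 2 × 6.183/0.5177 = 23.9, so 24, and 24/0.8 = 30 exactly. With the t distribution, 24 gives 79.1% one-sided, so 25 are needed, and 25/0.8 = 31.25, so 32. The exact match depends on the normal approximation.
- Two-sided 0.05, no dropout allowance: 30.3, which rounds to 30 if rounded to the nearest whole number (31 if rounded up).

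**3. Two-sided unadjusted power at the stated size.** Normal approximation: power = Φ(d√(n/2) − 1.960).

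| Analysed per group | Normal | t |
|---|---|---|
| 24 (30 × 0.8) | Φ(2.492 − 1.960) = 70.3% | 68.4% |
| 30 (nobody lost) | Φ(2.787 − 1.960) = 79.6% | 78.2% |

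**4. Difference detectable with 80% power at 24 per group.** Normal: 2.8016 × 8.2 × √(2/24) = 6.6 points. With the t distribution: 6.8 points.

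**5. What baseline adjustment would have to supply.** If adjustment reduces the SD by the factor √(1 − r²), where r is the correlation between baseline and change, then 80% power for 5.9 points at 24 per group needs a residual SD of 7.30 (normal) or 7.14 (t).
- Normal: |r| = √(1 − (7.30/8.2)²) = 0.46.
- t: |r| = √(1 − (7.14/8.2)²) = 0.49.

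As a guide, normal-approximation power at 24 per group is 72% for r = 0.2, 78% for r = 0.4 and 82% for r = 0.5.

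**The case against.** Three arguments against this deserve an answer.

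*Analysis of covariance may recover the power.* Section 2.9 plans it, and a correlation of about 0.46 to 0.49 in absolute value would restore 80% at 24 per group. That is possible. But section 2.7 states no correlation and works from raw mean changes and one SD. The planned analysis may have more power than the unadjusted figure, yet the article's calculation does not show it.

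*Not every dropout is lost to the analysis.* The full analysis set needs dosing and at least one primary measurement, and a patient who leaves after week 4 still contributes to the 4-week comparison. This stands: 24 per group is the planning case and not a certainty. It moves unadjusted power up towards 78 to 80%, but even full retention falls just short of 80%.

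*The SD is loosely described.* The wording speaks of SCORAD scores, not changes, and the source study is not at hand. Reading 8.2 as the SD of change is an assumption, though the natural one: it is the only SD given and it sits beside mean changes.

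A reader might also infer that the authors must have used a one-sided test. The documents do not support that. Leaving out the dropout step from a two-sided calculation lands on 30.3, and the exact one-sided match disappears when the t distribution is used.

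**Conclusion.** The point holds as an inconsistency within section 2.7. Its own inputs require 31 to 32 evaluable per group and 78 to 80 randomised, against the 60 stated. The cause is open between a one-sided calculation and an omitted dropout allowance. Either one contradicts a sentence that claims both a two-tailed test and a 20% allowance, so the correction does not depend on which slip occurred.

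Under the article's inputs, unadjusted two-sided power is 68% (t) to 70% (normal) with 24 analysed per group, about 10 to 12 percentage points below the stated 80%. It is tempting to call this the trial's true power, but that goes too far. The figure assumes that 8.2 is the SD of change, that the comparison is unadjusted and that the full 20% are lost to the analysis. Better retention or a useful baseline correlation would raise it. The firm conclusion is that the 80% claim does not follow from what section 2.7 states, and nothing elsewhere in the article repairs it.

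**What to change.** Keep 60 patients and correct section 2.7. Possible wording: *Sixty participants will be randomised; with 20% dropout about 48 will be evaluable. This gives about 68% power (unadjusted t-test, two-sided 0.05) for a 5.9-point difference in mean SCORAD change with an SD of change of 8.2, or 80% power for a 6.8-point difference.* If the normal approximation is preferred, the matching pair is 70% and 6.6 points. The two methods should not be mixed in one sentence.

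If the sponsor wishes to credit the planned analysis of covariance, section 2.7 should state and justify the assumed correlation between baseline and change; 80% at 24 per group needs about 0.46 (normal) to 0.49 (t) in absolute value. In either case, remove the claim that 30 per group gives 80% two-tailed power with the dropout allowance included, and bring the 80% in section 2.8 into line.

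Raising the total to 78 to 80 would also restore consistency. But section 2.2.1 says that recruitment began in September 2017, and correcting the statement does not require more patients. The cost of the wording change is a less favourable stated power.

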### Statistical analysis

2.8

Appropriate statistical analysis methods will be used according to the type of measurement, number of associated factors and associations, as well as the distribution status. The software that will be used for statistical analysis is the SAS version 9.3 for Windows, at a statistical significance level of 0.05 and statistical power of 80%.

### Efficacy assessment

2.9

As assigned, the Intent-to-treat (ITT) group comprises participants who will consume the trial product at least once, from the time of random assignment. The data for efficacy assessment will be mainly based on the full analysis set (FAS) group. However, additional analysis will be performed on the per protocol (PP) group. The FAS group is composed of participants who will consume the trial product after randomization and undergo at least 1 recorded measurement of primary efficacy assessment variables. On the other hand, the PP group is composed of all ITT participants who will complete the clinical trial without major violations of the study protocol.

For efficacy assessment, paired *t-*tests will be performed to compare measurements at weeks 4 and 8 to those recorded at baseline in order to assess the statistical significance of the changes within the treatment group. Inter-group comparisons will be performed via an analysis of covariance with an adjusted baseline. In order to assess the differences between the 2 groups with regard to trend changes after each visit, a repeated measures analysis of variance will be performed. Differences within groups before and after the intervention will be comparatively assessed via either paired *t*-tests or Wilcoxon signed rank tests.

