### Study aims and hypothesis

1.2

The primary aim of this study is to evaluate the efficacy and safety of SSHT versus placebo for the treatment of AD patients with gastrointestinal disorders in randomized clinical trials. We hypothesize that SSHT is more effective than placebo for the treatment of AD patients with gastrointestinal symptoms. To assess the efficacy and safety of SSHT, a randomized, double-blinded, and placebo-controlled trial will be conducted.

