### Safety assessment

2.10

The data for safety assessment of the trial product will be based on the safety group. The safety population (SP) group is composed of all participants who will undergo at least 1 intervention and post-intervention safety assessment.

Adverse events: either the Chi-square or Fisher exact test will be performed to compare the differences between groups, and a summary sheet for each body organ will be created. In addition, the incidence rate of adverse events that are confirmed to be associated with either the trial product or the placebo product will be comparatively assessed using the same method.Laboratory test values: after completion of the trial, the fraction of incidences that exhibit clinical test values exceeding the normal range will be assessed using either Chi-square or Fisher exact test.Vital signs: means and standard deviations for blood pressure and heart rate will be recorded at each visit. Furthermore, significant changes in the categories of vital signs between the start and the end of the intervention will be assessed using either paired *t* tests or Wilcoxon signed rank tests.

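### Within-arm before-after tests are listed as efficacy tests beside the valid between-group ANCOVA, with no statement of which decides efficacy, and they are the only test named for mean vital signs

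*Protocol article*

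**What the plan says.** The hypothesis in section 1.2 is comparative: "We hypothesize that SSHT is more effective than placebo for the treatment of AD patients with gastrointestinal symptoms".

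Section 2.9 names four pieces of analysis in one paragraph:

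- Paired t-tests of weeks 4 and 8 against baseline, "in order to assess the statistical significance of the changes within the treatment group".
- An analysis of covariance between groups, adjusted for baseline.
- A repeated measures analysis of variance for group differences in trend over visits.
- A second mention of within-arm testing: "Differences within groups before and after the intervention will be comparatively assessed via either paired" t-tests or Wilcoxon signed rank tests.

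All stand under the efficacy heading, and section 2.8 sets a general significance level of 0.05. No sentence says which of them decides whether SSHT works. The ANCOVA sentence does not name a time point, although section 2.7 plans on the change after 4 weeks.

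For safety, section 2.10 compares adverse events between groups by Chi-square or Fisher exact test. For blood pressure and heart rate it gives means and standard deviations by visit, and then: "significant changes in the categories of vital signs between the start and the end of the intervention will be assessed using either paired" t-tests or Wilcoxon signed rank tests. No comparison of mean vital signs between arms is named.

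**The concern.** A within-arm paired test asks whether the mean changed from baseline in that arm. The trial asks whether SSHT changes SCORAD more than placebo does. The protocol itself expects a sizeable change on placebo, and both arms receive 1% hydrocortisone acetate (sections 2.3 and 2.4) for a disease that the Introduction describes as chronically relapsing. A significant before-after change in the SSHT arm is therefore expected whether or not SSHT does anything.

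Without a stated order among the tests, the plan leaves open how to read a trial in which the ANCOVA shows no difference but the SSHT paired test is significant, or in which one arm is significant and the other is not. Neither pattern is a test of the difference between arms.

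For mean vital signs, a start-to-end shift may be a drug effect or may be something that happens to everyone over four weeks. Only the placebo arm can separate the two, and the named tests do not use it.

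**Working it through.** **Inputs.** All are from section 2.7. The assumed mean SCORAD changes at 4 weeks in the SSHT and placebo groups are "13.8 (μt) and 7.9". The spread is given as "the standard deviations of the SCORAD scores between 2 groups were 8.2". The test is two-sided at 0.05, with 30 per arm and 20% dropout, so 30 × 0.8 = 24 evaluable per arm.

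**The plan's own sample size.** Between arms, the difference is 13.8 − 7.9 = 5.9. The usual formula gives n = 2 × [8.2 × (1.960 + 0.842) / 5.9]² = 30.3, so 31 evaluable per arm, and 31 / 0.8 = 38.75, so 39 per arm after dropout. The stated 30 per arm is not reproduced with a two-sided test; a one-sided 0.05 does give 24 evaluable and 30 recruited. This is a separate matter. The point here does not depend on it, and the check uses both 24 and 30.

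**Within-arm test when SSHT adds nothing.** Let the true change be 7.9 in both arms. The paired t-test has noncentrality δ = 7.9 / (s / √n), where s is the SD of change, and power P(|T| > t(0.975, n − 1)) under the noncentral t.

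- n = 24, s = 8.2: δ = 7.9 / (8.2 / √24) = 7.9 / 1.674 = 4.72; power 99.5%.
- n = 30, s = 8.2: δ = 7.9 / (8.2 / √30) = 7.9 / 1.497 = 5.28; power 99.9%.

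The arms are independent, so the chance that both are significant is the square: 98.9% and 99.8%.

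**If 8.2 is the SD of raw scores.** The wording allows this. Then s = 8.2 × √(2(1 − r)), where r is the baseline-to-week-4 correlation. The documents do not give r, so a range is assumed.

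| Reading of 8.2 | s | n = 24: one arm / both | n = 30: one arm / both |
|---|---|---|---|
| SD of change | 8.20 | 99.5% / 98.9% | 99.9% / 99.8% |
| SD of scores, r = 0 | 11.60 | 89.2% / 79.5% | 95.0% / 90.3% |
| SD of scores, r = 0.3 | 9.70 | 96.8% / 93.8% | 99.1% / 98.1% |
| SD of scores, r = 0.5 | 8.20 | 99.5% / 98.9% | 99.9% / 99.8% |
| SD of scores, r = 0.7 | 6.35 | >99.9% / >99.9% | >99.9% / >99.9% |

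**Contrast with a between-group test.** In 100,000 simulated trials with a true change of 7.9 and SD 8.2 in both arms, the two-sample t-test on change rejected in 5.1% (n = 24) and 5.0% (n = 30), as it should.

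**Significance in one arm only.** At the weakest setting above (n = 24, r = 0), SSHT alone would be significant with probability 0.8916 × (1 − 0.8916) = 0.097, although the arms are identical.

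**Vital signs.** No arithmetic is possible, because no planning values are given. Section 2.10 names a between-group test for adverse events and for out-of-range laboratory values, but only a start-to-end test for vital-sign means. Section 2.13 says that clinically significant vital-sign abnormalities are recorded as adverse events, so those do reach the between-group comparison. Smaller mean shifts do not.

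**The case against.** The strongest reply is that the right analysis is already in the plan. The ANCOVA and the repeated measures ANOVA are both between-group, and so are the hypothesis and the sample size. The paired tests are described as assessing change within a group, and nothing says that they will settle SSHT against placebo. This stands. A reader might infer that the trial intends to judge SSHT by its before-after change; the document does not support that. Listing the paired tests first is sentence order, not a hierarchy, and a detailed order of analyses may sit in an analysis plan that is not shown. What remains is that the article itself places within-arm significance tests under efficacy and leaves their role open.

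A reader might also carry the 99% figure over to week 8, the secondary outcomes or vital signs. The planning values cover SCORAD at 4 weeks only, so it cannot be extended.

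Nor can it be said that vital signs lack any concurrent comparison, because clinically significant abnormalities are compared as adverse events. The visit-wise means and SDs also mean that the data for comparing arms will exist.

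Finally, regression to the mean and the hydrocortisone are plausible sources of change in both arms, but the documents do not size them. SCORAD entry is bounded on both sides (15 to 49), and the ointment is supplied at screening, up to two weeks before visit 1. If visit 1 is the baseline, part of either effect may have passed. The calculation needs neither explanation, only the protocol's own assumed placebo change.

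**Conclusion.** The point holds in a limited form. Section 2.9 assigns within-arm tests to efficacy beside a valid between-group analysis without saying which decides. For SCORAD at week 4, such a test carries no information on SSHT against placebo: at the planning values it is significant in about 99% of trials with no SSHT effect beyond placebo. With 24 per arm this becomes about 89% to 99% if 8.2 is the SD of raw scores and r lies between 0 and 0.5. These figures assume normally distributed changes, a true placebo change of 7.9, and 24 to 30 evaluable children per arm.

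For mean blood pressure and heart rate, the only named test cannot separate a drug effect from a time effect. That conclusion rests on the design of the test and not on the calculation.

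The planned ANCOVA remains sound, so this does not undermine the trial's ability to answer its question. It is a stated method that should be given its proper role before the data are analysed.

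**What to change.** 1. In section 2.9, state that the baseline-adjusted between-group ANCOVA of SCORAD at week 4 alone decides efficacy.
2. Report within-arm changes at weeks 4 and 8 as means with 95% confidence intervals, labelled descriptive and without p-values. Delete both mentions of paired and signed rank tests as efficacy tests.
3. In section 2.10, replace the paired vital-sign tests with a between-group comparison of end-of-treatment values adjusted for the start value, reported as a difference with its 95% confidence interval. Keep the visit-wise means and SDs and the adverse-event comparison as they are.

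The cost is wording and table shells, plus the loss of the within-arm p-values. No new data, visits or participants are needed.

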### Study phase

2.3

When patients visit the trial center for the screening process, they will undergo different assessments, including blood and urine tests, and answer a survey questionnaire on AD symptoms by which the investigator may determine the patient's eligibility to participate in this clinical trial. At the screening visit, Lacticare (hydrocortisone-acetate 1% (100 g)) will be provided as a control variable which is the conventional therapy of AD to all participants. The amount and frequency of ointment usage from the screening visit to visit 3 (8-week time point) will be recorded. Patients found eligible to participate will be informed of their eligibility via a telephone call, and selected participants will be asked to visit the trial center (visit 1) within 2 weeks of the screening examination for random assignment into either the experimental group or the control group. After the assignment, the participant will undergo additional assessments (answering survey questionnaires including those on AD, as well as a physical examination) and will receive enough of the trial product for 4 weeks (to be used 3 times per day). After 4 weeks, participants will be asked to return for visit 2 to perform identical assessments (survey questionnaires and blood tests). For the following 4-week period, the participants will be asked to stop the usage of all medication, with the exception of Lacticare, and return for visit 3 after 4 weeks to undergo the same assessment. Detailed assessment types and the schedule used are outlined in Table 1.

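### The set labelled ITT requires a dose, and the repeated-measures ANOVA over visits drops children with a missing visit and does not isolate the 4-week effect

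*Protocol article*

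**What the plan says.** All references are to the protocol article.

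- **Analysis sets (Section 2.9).** The first set is defined so that "the Intent-to-treat (ITT) group comprises participants who will consume the trial product at least once". Efficacy rests mainly on the FAS, whose members must have taken the product and must "undergo at least 1 recorded measurement of primary efficacy assessment variables". The text does not say whether a baseline value is enough. The per-protocol set is drawn from the ITT set.
- **Tests (Section 2.9).** Groups are compared by a baseline-adjusted analysis of covariance. Separately, to assess "differences between the 2 groups with regard to trend changes after each visit, a repeated measures analysis of variance will be performed".
- **Visits (Sections 2.1 and 2.3).** Product is taken for 4 weeks, with visits at weeks 4 and 8. Between those visits "the participants will be asked to stop the usage of all medication, with the exception of Lacticare". Week 8 is therefore an off-treatment visit.
- **Sizing (Section 2.7).** The assumed "mean changes of the SCORAD score in the SSHT and placebo groups after 4 weeks of intervention were 13.8 (μt) and 7.9", and "the standard deviations of the SCORAD scores between 2 groups were 8.2". The test is at a "significance level of 0.05 in 2-tailed test", and a 20% dropout rate is allowed for.

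**The concern.** Two features of Section 2.9 work against the question the trial was sized to answer.

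First, ITT normally means everyone randomised. Here it means everyone dosed, and the FAS and per-protocol sets are narrower still. A reader of the results would take the label for something it is not.

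Second, a classical repeated-measures ANOVA needs a complete row for each child. A child seen at week 4 but not at week 8 has the very outcome used in Section 2.7, yet is left out. If the test covers all scheduled visits, it also combines a visit at the end of treatment with one four weeks after treatment stopped. A significant or non-significant result then says little about the 4-week effect, and nothing separately about what remains after stopping.

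**Working it through.** **1. The plan's own figure.** Section 2.7 gives a difference of 13.8 − 7.9 = 5.9 and an SD of 8.2, for a two-sided 0.05 test with 80% power. Per arm, n = 2 × [8.2 × (1.960 + 0.842) / 5.9]² = 30.3, rounded up to 31. Allowing for 20% loss, 31 / 0.8 gives 39 per arm, or 78 in total. The stated 60 is not reproduced; that is a separate matter. For this point, the target is 5.9 at week 4, and 20% loss from 30 per arm leaves 0.8 × 30 = 24.

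**2. Who enters which analysis.**

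| Child | Set called ITT | FAS | Week-4 ANCOVA | Classical repeated-measures ANOVA, weeks 0/4/8 |
|---|---|---|---|---|
| Randomised, never dosed | no | no | no | no |
| Dosed, lost before week 4 | yes | only if baseline counts | no outcome | dropped |
| Dosed, seen at week 4, not at week 8 | yes | yes | kept | dropped |
| Dosed, seen at both | yes | yes | kept | kept |

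The third row is where the choice of trend test loses usable data.

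**3. What the group effect estimates.** Over baseline, week 4 and week 8, the expected group effect is (0 + 5.9 + e8) / 3, where e8 is the effect left at week 8. The documents do not give e8, so a range is shown:
- none left: 5.9 / 3 = 1.97
- half left: (5.9 + 2.95) / 3 = 2.95
- all left: (5.9 + 5.9) / 3 = 3.93

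None of these equals 5.9.

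**4. Power by arithmetic.** Assumptions: 24 per arm, SD of change 8.2, compound symmetry, correlation 0.5 (so the SD at each visit is also 8.2), half the effect left at week 8.
- Group effect: SD of the three-visit mean = 8.2 × √[(1 + 2 × 0.5) / 3] = 6.70. SE = 6.70 × √(2/24) = 1.93. 2.95 / 1.93 = 1.53, so power ≈ Φ(1.53 − 1.96) = 33%.
- Week-4 ANCOVA: residual SD = 8.2 × √(1 − 0.5²) = 7.10. SE = 7.10 × √(2/24) = 2.05. 5.9 / 2.05 = 2.88, so power ≈ Φ(2.88 − 1.96) = 82%.

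**5. Power by simulation** (4,000 runs, same assumptions except as shown):

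| Correlation | Effect at week 8 | Week-4 ANCOVA | Group-by-time | Group effect |
|---|---|---|---|---|
| 0.5 | 2.95 | 80% | 60% | 32% |
| 0.7 | 2.95 | 75% | 60% | 19% |
| 0.5 | 0 | 80% | 72% | 17% |

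If the full effect lasts to week 8 (correlation 0.5), the group effect still reaches only 51%, because baseline is averaged in. If the test used only weeks 4 and 8, with SD 8.2 at both and half the effect left, the averaged effect would be (5.9 + 2.95) / 2 = 4.4, with power of 53% to 58% for correlations of 0.7 to 0.5.

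Every test in the table uses the same complete 24 per arm. The gaps come from the hypothesis tested, not from deleted children.

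**6. What dropping incomplete rows can do.** In a separate check, 23% of children were lost between weeks 4 and 8, with loss depending on the week-4 result (assumed correlation 0.6). The week-4 effect among children with both visits was 5.2, against 5.9 with all week-4 data kept: a shift of 0.7, or 0.7 / 5.9 = 12%.

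**7. What a mixed model cannot do.** In five simulated trials (30 per arm, 20% monotone dropout), a mixed model with a common baseline mean and unstructured covariance gave the same week-4 estimate as ANCOVA on children with week-4 data, to three decimals. A child with only a baseline value adds nothing to that contrast.

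**The case against.** The strongest reply is that the ANCOVA is already the named between-group comparison, and that read with Section 2.7 it is naturally a week-4 test. The repeated-measures ANOVA is an additional look at trends and was never meant to estimate a week-4 contrast. This stands: the plan does not lose the tabulated power on its 4-week question, and the power figures only show that the trend test is no substitute for the ANCOVA. It is also right that group-by-time compares profiles and does not average them.

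A reader might infer more: that the FAS confines efficacy to children who return, that the expected 20% dropouts are discarded, and that the result is inflated by a known amount. The documents do not support this. The FAS wording does not require a post-baseline value. Section 2.7 does not say when dropouts occur, and a child leaving after week 4 stays in a week-4 ANCOVA. The 12 of 60 is therefore an upper bound. If all SSHT losses fell before week 4, those children would have changed exactly as on placebo, and the completer effect were 5.9, the all-randomised effect would be 0.8 × 5.9 = 4.72, an overstatement of 5.9 / 4.72 = 1.25, or 25%. That illustrates an assumption and is not a result of the plan.

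Few children may go undosed, since product is handed over at the randomisation visit under blinding. That makes the ITT label a small error in numbers, but still a wrong label. Finally, missing-data sensitivity analyses are commonly left to a statistical analysis plan, so their absence is not a fault here.

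**Conclusion.** The point holds in a limited form. The set called ITT is a dosed set, and no efficacy set covers all randomised children. The FAS measurement is ambiguous. The repeated-measures ANOVA in its classical form discards children who have the week-4 outcome, and over all visits neither of its tests isolates the 4-week effect.

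The size rests on assumptions about correlation and about what remains at week 8: for the cases tabulated, 60% to 72% power for group-by-time and 17% to 32% for the group effect, against 75% to 80% for the week-4 ANCOVA. The effect of dropping incomplete rows was 5.2 against 5.9 in one assumed pattern of loss. If the full plan already fits a mixed model under the repeated-measures name, the deletion part falls away; the need for separate visit contrasts and the labelling point remain. The main ANCOVA is not undermined.

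**What to change.** - Keep the baseline-adjusted ANCOVA at week 4 as the test of the effect the trial was sized on.
- Replace the repeated-measures ANOVA by a likelihood-based mixed model (PROC MIXED in the SAS already named in Section 2.8). Use SCORAD at baseline, week 4 and week 8 as responses, a common baseline mean, group-by-visit terms, unstructured covariance, and separate week-4 and week-8 contrasts. Include all randomised children, as randomised, with any SCORAD.
- Rename the dosed set modified ITT, and state whether the FAS measurement must be post-baseline.
- Optionally, add a placebo-based imputation sensitivity analysis for children lost before week 4, whose bias the mixed model cannot remove.

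The gain is that partial data are kept and on- and off-treatment effects are reported separately. The cost is wording and a little programming, with no change to conduct. The estimate may come out slightly less favourable, although in the check above keeping all week-4 data moved it the other way.
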